##### Phase 2: Targeted exercise interventions

1. Age between 21 and 65 years;
2. Chronic thoracic SCI (levels C2-T12; more than 12 months since injury);
3. AIS grades C or D or volitional strength of at least 1/5 in two or more key lower extremity muscles; or some participants with electromyographic evidence for residual motor circuits;
4. Strength of at least 3/5 in shoulder and elbow muscles;
5. Able to tolerate standing with support;
6. Morphologically capable of fitting a weight-support harness and robotic treadmill system: measurements of the greater trochanter to lateral epicondyle between 35-47 cm for placement in the thigh cuffs; pelvic width >50 cm; thigh circumference above the knee <57 cm; and body mass <135 kg.

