**Baseline testing (to be conducted over two visits):**

Once a participant has provided signed informed consent, a detailed review of the participant’s history and medical record will be conducted. A physical exam will be performed, including the Modified Ashworth Scale, the Spinal Cord Assessment Tool for Spasticity (SCATS) (Benz et al. 2005), and the American Spinal Injury Association (ASIA) Impairment Scale (AIS). Further clinical assessments will include the Berg Balance Scale; the Walking Index for Spinal Cord Injury II; the 10-meter walk test; the 10-second seated step test; a modified grasp-and-release test (Wuolle et al., 1994); pinch dynamometry; the Spinal Cord Injury Spasticity Evaluation Tool (SCI-SET) (Adams et al. 2007); the WHOQOL-BREF questionnaire (World Health Organization 1998); SCI-QoL questionnaire (Tulsky et al. 2011); and the

McGill Pain Questionnaire (short form). Depending on the severity of paraparesis, not all Participants will be able to perform the step or walk tests. As such, no baseline walking data will be collected for these outcomes in these participants. To ensure tolerance of upright position, heart rate and blood pressure will be measured for 10 minutes while the Participant is in an upright position supported using an overhead harness or standing frame. A full-body DXA scan will be performed. To be eligible for Phase 2 of the study, results from the DXA of the proximal femur must not have a T-score lower than 3.5SD below age/gender-matched controls. Seated and standing computerized posturography, motor evoked potentials, multiple tests of soleus H-reflex facilitation, and surface electromyography will also be assessed. At this point, the study evaluation is complete for participants with AIS A/B impairment. Only participants with AIS C/D injury or volitional strength of at least 1/5 in two or more key lower extremity muscles or some participants with electromyographic evidence for residual motor circuits will be eligible for the interventional component of our study. If any exclusion criteria are met, or if the participant decides at any time not to continue, he or she will not be further studied.

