### **Primary outcomes:**

1. Change from baseline in motor evoked potential amplitude in the tibialis anterior muscle; change from baseline in AIS lower extremity motor score.

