### **Statistical Analysis:**

For the observational phase, exploratory analyses will be undertaken to determine how well scores on the electrographic outcomes (evoked potentials, H-reflex testing, computerized posturography, surface electromyography) correlate with clinical outcomes such as gait disability, gait speed, and AIS motor and sensory scores. Using post hoc regression analysis, we hope to generate a preliminary model to predict anatomical and functional integrity of specific neural tracts based on performance on this battery of tests. This analysis and any resulting predictive model would need further validation with a prospectively studied population. The interventional phase of the study would not depend on the success of obtaining such a predictive model.

For the interventional phase of the study, participants will be randomly assigned to receive either locomotor training followed by multimodal training, or multimodal training followed by locomotor training. The primary outcomes will be change in tibialis anterior motor-evoked potential amplitude and change in lower extremity motor score (LEMS) compared to baseline. All other outcomes are secondary and exploratory.

The most rigorous method of analyzing data from crossover studies involves the use of independent-sample rather than paired-sample tests (Wellek & Blettner 2012). Therefore, outcome measures will be calculated within each subject as the percent change between baseline and completion of each intervention. The percent change across all subjects for each training modality will be compared using independent-sample t-tests or Mann-Whitney U tests depending on the normality of the data distribution. To test for the possibility that the washout period does not fully eliminate carryover effects, the percent change across all subjects for each training period (pre-washout, post-washout) will also be compared using independent sample tests. Statistical significance for all outcomes will be corrected for multiple comparisons using Bonferroni's method.

**Power Calculation:** Given that our training protocol is novel, we need to make predictions by extrapolating from other types of protocols. This is further hampered by the fact that most SCI

rehabilitation studies involve rather small numbers of participants in often inadequately controlled studies.

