- McGill Pain Questionnaire (short form) – Chronic neuropathic pain commonly plagues subjects with SCI. This short (less than 5 minutes), validated survey will provide a baseline to track whether any neural plastic changes result in adverse effects on neuropathic pain.
- Spinal Cord Injury Spasticity Evaluation Tool (SCI-SET) - This survey evaluates how spasticity impacts a person's activities of daily living over the course of the previous 7 days. The survey uses a bidirectional Likert scale to detect both negative and positive impacts of spasticity (Adams et al. 2007).
- SCIQoL - Participants will complete a questionnaire regarding physical/medical health, emotional health, physical function, and social participation. A research assistant will conduct the interview. The questionnaire is located on an online platform called Assessment Center. The Assessment Center database is housed at Northwestern University and analyzed by a team at the University of Michigan. No HIPAA identifiers will be collected through the online platform.
- WHOQOL-BREF Questionnaire – This tool assesses general quality of life, and has been internationally validated for use in the SCI population. It is briefer than the computer-adapted SCI-QOL survey and will be used specifically to correlate with findings on the SCI-SET and SCATS (World Health Organization 1998).

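### Percent change is the analysis scale for every outcome, but the co-primary LEMS can start at 2 or even 0, where that scale is unstable or undefined

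*Protocol*

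**What the plan says.** Section 3, Statistical Analysis, names two primary outcomes for the interventional phase: change in tibialis anterior MEP amplitude and "change in lower extremity motor score (LEMS) compared to baseline". The next paragraph sets the scale: "outcome measures will be calculated within each subject as the percent change between baseline and completion of each intervention". It then sets the test: "The percent change across all subjects for each training modality will be compared using independent-sample t-tests or Mann-Whitney U tests", chosen by normality. The scale is not limited to any one outcome, and nothing is said about zero, very small or negative starting values.

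The Phase 2 inclusion criteria list the entry routes: "AIS grades C or D or volitional strength of at least 1/5 in two or more key lower extremity muscles; or some participants with electromyographic". The quotation stops inside the last route, which rests on signs of surviving motor pathways in the electromyogram. The same routes appear in section 1 (Interventional Phase), under Baseline testing, and in the inclusion list repeated in section 3a. The summary statement that opens the procedures in section 3a leaves the electromyographic route out.

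Under Clinical Tests, modified Ashworth runs from 0 to 4 and WISCI II from 0 to 20. Of SCI-SET the protocol says: "The survey uses a bidirectional Likert scale to detect both negative and positive impacts of spasticity". Both exclusion lists bar interventional participants whose tibialis anterior MEP cannot be detected at baseline.

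**The concern.** Percent change divides by the starting value. For LEMS, the entry criteria let that value be very small and, by one route, zero. The protocol guards the MEP denominator at study entry but has no such guard for LEMS. Followed as written, the rule has two consequences for a primary outcome:

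- A participant with LEMS 0 has no value, and the analyst would have to settle how to handle that person without guidance from the protocol.
- Among the others, the same gain in points counts many times more in a weak participant than in a strong one. With about 18 completers, a few low starters can drive the comparison.

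The percent-scale planning figures in the Power Calculation concern MEP amplitude. Nothing in the protocol supports a percent scale for LEMS.

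**Working it through.** **1. The plan's own figure.** Inputs from the Power Calculation: 50% versus 25% improvement, spread 25% (called a variance, read here as an SD), two-sided α = 0.05, 18 subjects. Each completer supplies one value per modality, so n = 18 per modality. The noncentrality is 25 / (25 × √(2/18)) = 3.0 on 34 degrees of freedom, and power is 0.83. Enrolment is 18 / (1 − 0.25) = 24. The stated power above 80% is reproduced. It concerns MEP only and presumes a usable percent change in every completer.

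**2. What one LEMS point is worth.** The percent change for a one-point gain from baseline b is 100 / b. The strength route requires "volitional strength of at least 1/5 in two or more key lower extremity muscles", so the lowest score it allows is 1 + 1 = 2. The electromyographic route states no leg-strength minimum, so 0 is allowed.

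| Baseline LEMS | One-point gain |
|---|---|
| 0 | undefined |
| 2 | 50% |
| 5 | 20% |
| 10 | 10% |
| 20 | 5% |
| 40 | 2.5% |

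One point at LEMS 2 weighs 50 / 2.5 = 20 times as much as one point at LEMS 40. It also equals the whole improvement projected for multimodal training on MEP.

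**3. Secondary scales.** Ashworth and WISCI II include 0, so the same division fails for anyone starting there. SCI-SET can be zero or negative. As an illustration, a move from −1 to +1 gives 100 × (1 − (−1)) / (−1) = −200%, so a rise in the score is recorded as a fall.

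**4. Illustrative power for LEMS.** The protocol gives no LEMS distribution, gain or SD, so every input here is assumed: 18 values per modality, whole-number scores limited to 0-50, baselines uniform over the stated range, two-sided α = 0.05.

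| Assumed gains | Baselines | Absolute change, t | Percent change, t | Percent change, rank-sum |
|---|---|---|---|---|
| Additive: 4.5 vs 2 points, SD 2.5 | 2-45 | about 0.82 | 0.30 | 0.59 |
| Additive, same | 10-45 | 0.82 | 0.66 | 0.70 |
| Additive, same | 20-45 | about 0.82 | 0.76 | 0.75 |
| Proportional: 50% vs 25%, SD 25% | 2-45 | 0.55 | 0.71 | 0.66 |
| Proportional, same | 2-30 | 0.57 | 0.81 | 0.79 |

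With additive gains the loss comes almost entirely from low baselines. With proportional gains over ranges that include low baselines, percent change has the higher power.

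**The case against.** The strongest reply has four parts.

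**MEP is protected.** The MEP exclusion rules out a zero denominator at study entry, and the planning figures for MEP are themselves percent changes. This stands, so the point is not about MEP. The exclusion does act only at entry, and very small amplitudes can still make the ratio noisy.

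**LEMS 0 is an edge case.** It needs the electromyographic route, which is open only to some participants, who must also have a detectable MEP, tolerate supported standing and meet the arm-strength criterion. One summary in section 3a omits the route. Randomization and Research Design describe the group as motor-incomplete. This limits how often the value is undefined, and the documents do not let that number be estimated. It does not remove the instability at LEMS 2 and just above, which the strength route allows.

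**Mann-Whitney is available for non-normal data.** It limits outliers, and its figures are closer than the t-test figures to what the plan would do with skewed data. It cannot rank a value that does not exist, and it still ranks gains after division by baseline.

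**An unseen analysis plan may add a zero rule.** It may, but the scale itself is a choice that the protocol states for a primary outcome.

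A reader might also infer three things that the documents do not support:

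- *The primary outcome definition contradicts the analysis section.* The definition reads "change from baseline in AIS lower extremity motor score". Change is a general term there, and Statistical Analysis uses it too before specifying percent.
- *The percent scale causes the missing walk and step data.* That gap follows from Baseline testing, which collects no value when the test cannot be done; absolute change would be missing too.
- *SCATS and the McGill questionnaire can start at 0.* The protocol gives no numerical range for either.

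**Conclusion.** The point holds for LEMS and, with less weight, for modified Ashworth, WISCI II and SCI-SET, which the protocol labels secondary and exploratory. The undefined value at 0 and the contrast of 50% with 2.5% follow from the entry criteria and need no assumption about data.

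The size of any power loss is not established. It would be tempting to conclude that power for LEMS falls from about 82% to 30%. That needs gains unrelated to baseline, baselines reaching down to 2, and a t-test on skewed data. Raising the lowest baseline to 20 leaves about 76% (t-test) or 75% (rank-sum), and proportional gains with low baselines reverse the ranking. Nor does the protocol say that participants with LEMS 0 are dropped; it is silent on them.

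This should be fixed. It does not undermine the MEP sample-size calculation.

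**What to change.** In section 3, Statistical Analysis, restrict percent change to tibialis anterior MEP amplitude, preferably analysed as log(end/start) and back-transformed to a percent. State that LEMS and the ordinal, count and signed scale outcomes are analysed as absolute change from the start of each training period. Reconcile the summary in section 3a with the inclusion lists on the electromyographic entry route, so that the lowest possible LEMS is clear.

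The cost is analysis wording. Sample size, training and visits stay as they are, and MEP results can still be read against the 50% and 25% planning figures. The one downside is some loss of power for LEMS if its gains are truly proportional to baseline.

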### **Post-training evaluation:**

All the measures evaluated at the baseline visits will be repeated at the beginning and end of each training period. Evaluation will take place over one or two sessions within one week of the completion of each intervention.

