The most applicable study upon which to base our power analysis measured MEP amplitudes before and after 60-100 sessions of treadmill training in eight subjects with incomplete thoracic SCI (Thomas & Gorassini 2005). They found a  $46 \pm 12\%$  increase in maximal MEP amplitude post-training. Additionally, studies in uninjured volunteers demonstrated a 40-70% increase in MEP amplitudes with skilled training exercises but not passive movement or strength training (Jensen et al. 2005; Perez et al. 2004).

Due to these and other factors, we project an improvement of 50% with MULTIMODAL training versus 25% with TREADMILL training. The use of a crossover design will reduce inter-subject variability between the two training modalities compared to a parallel-group design. We conservatively project an estimated variance of 25% for each group – this magnitude of variance is larger than the average variance seen in the MEP studies cited above. Based on these numbers, the calculated power to detect a difference between the two training groups on a two-tailed independent-sample *t*-test or Mann-Whitney test is greater than 80% with 18 subjects, at an  $\alpha = 0.05$ . We will enroll 24 subjects to account for up to a 25% dropout rate.

|                | Year 1 | Year 2 | Year 3 | Total N |
|----------------|--------|--------|--------|---------|
| Phase 1 | 15     | 18     | 18     | 51      |
| Phase 2 | 6      | 10     | 8      | 24      |

**Table 3** Clinical Study Timeline – Participants enrolled per year.

**3a. Basic Information** (Even if described under “Procedures”, list the information requested below where pertinent.)

The study will occur in two phases: An observational phase, in which participants will undergo a series of clinical and neurophysiological tests; and an interventional phase, in which participants with incomplete SCI will undergo standard LOCOMOTOR training and experimental MULTIMODAL training in random order. Training will continue for 48 sessions per intervention, separated by a 6-week washout period. The clinical and neurophysiological tests will be repeated at the end of each intervention.

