To minimize the risk of fracture, participants will undergo bone density scans by dual x-ray absorptiometry (DXA) prior to participation/enrollment. Potential participants with density <3.5 SDs below the norm for lower extremity bone density will be excluded from participating in the Interventional Phase of the study. The amount of radiation exposure from the DXA scan is minimal: We estimate all of the DXA measurements combined will sum up to approximately 35  $\mu$ Sv of radiation exposure per scan, or 140  $\mu$ Sv total (**Table 4**). Four routine chest X-rays would deliver an approximate dose of 240  $\mu$ Sv. In addition, the average New York City resident receives approximately 300 millirem/year (which converts to 3000  $\mu$ Sv/year). Therefore, these participants would have to repeat all of these tests more than 20 times to receive an equivalent dose.

To minimize fall risk, all seated and standing training and assessment protocols will be conducted with participants wearing a support harness attached to an overhead unweighing system as needed. The unweighing system includes a mechanism to prevent falls of more than four inches in any direction. At least two clinicians will be at the participant's side at all times to assess comfort and provide manual assistance/stabilization as necessary.

The surface electromyography-Brain Motor Control Assessment (BMCA) protocol involves recording the endogenous electrical potentials produced by the participant's muscles using skin electrodes. No current is applied toward the participant. The procedure is analogous to an electrocardiogram. Therefore, the risks are minimal, such as transient skin irritation at the sites of surface electrode application.

In contrast to the BMCA, H-reflex testing involves the use of surface electrodes *and* exogenously applied electrical stimuli. The resulting induced signals are then recorded with surface electrodes over the back, neck, and scalp. The applied currents are small (usually less than 50 milliamperes) but may be transiently irritating or painful. Superficial muscles near the stimulating electrodes may also twitch during stimulation, but this is not physically painful or dangerous. There is no risk of seizure from H-reflex stimulation.

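### The analysed percent change does not say where period 2 starts; if the study baseline is used, retained period-1 gain shrinks the contrast between the two trainings

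*Protocol*

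**What the plan says.** **Analysis variable and primary outcome.** Statistical Analysis defines the within-subject score as "the percent change between baseline and completion of each intervention". Primary outcomes defines MEP amplitude and lower extremity motor score as changes from baseline. Neither section names a reference for the second period.

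**What baseline means elsewhere.** The section on Baseline testing describes a two-visit assessment before randomisation. Post-training evaluation and 6-Week Follow-up evaluation both refer back to those visits.

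**Schedule.** Post-training evaluation states: "All the measures evaluated at the baseline visits will be repeated at the beginning and end of each training period". The Schedule item under Specific Aims says the same and adds the six-week follow-up. An assessment after washout and before period 2 is therefore planned. The summary in 3a, Basic Information, mentions less: "The clinical and neurophysiological tests will be repeated at the end of each intervention".

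**Power Calculation.** "we project an improvement of 50% with MULTIMODAL training versus 25% with TREADMILL training"; "We conservatively project an estimated variance of 25% for each group"; power "greater than 80% with 18 subjects" on a two-sided independent-sample test at 0.05.

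**Radiation.** Section 3b puts DXA at about 35 microSv "of radiation exposure per scan, or 140" microSv in total. It concludes that the tests could be repeated over twenty times before matching a year's background exposure of 3000 microSv.

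**The concern.** On the document's own use of the word, a period-2 change from baseline runs from before period 1. It then spans both trainings and the washout, and any period-1 gain still present is counted a second time, under the wrong training. Because each training comes second in one of the two sequences, both means are inflated. The weaker training is inflated more, since it inherits the larger gain. The contrast moves towards zero.

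The planned carryover check, which compares the two periods, is affected too. A retained gain alone would make period 2 look larger, even if each training worked equally well in both periods.

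Retention is plausible on the protocol's own terms. The proposed mechanism is new or stronger neural connections, and Statistical Analysis allows that the washout may be incomplete.

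**Working it through.** **Inputs from the protocol.** Gains of 50% (multimodal, M) and 25% (locomotor, L); 18 evaluable subjects; two-sided alpha 0.05. The stated variance of 25% is read as an SD of 25 points. Each subject contributes one score per training, so there are 18 observations per training, treated as independent as the plan does.

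**Assumptions.** Equal sequence sizes; a fraction r of the period-1 gain present at the start of period 2, with r from 0 to 1.

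**1. The plan's own figure.** Noncentrality λ = (difference / SD) × √(n/2) = (25/25) × √9 = 3, with 34 degrees of freedom. Power is 83.0% by noncentral t (85.1% by normal approximation, about 81% for Mann-Whitney at efficiency 0.955). The claim of more than 80% is reproduced. Reading 18 as a total, 9 per group, gives only 51.3%. A literal variance of 25 (SD 5) gives about 100%. Enrolment: 18 / 0.75 = 24, as stated.

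**2. Study baseline used for both periods, additive gains.**
- L first: L = 25, M = 50 + 25r.
- M first: M = 50, L = 25 + 50r.
- Means: M = 50 + 12.5r, L = 25 + 25r. Difference = 25 − 12.5r.

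**3. The same with multiplicative gains.**
- L first: M = 100 × [(1 + 0.25r) × 1.5 − 1] = 50 + 37.5r.
- M first: L = 100 × [(1 + 0.5r) × 1.25 − 1] = 25 + 62.5r.
- Means: M = 50 + 18.75r, L = 25 + 31.25r. Difference = 25 − 12.5r again.

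**4. Results, with SD held at 25.**

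| r | Difference | λ | Power (t) | Period 1 mean | Period 2 mean, additive / multiplicative |
|---|---|---|---|---|---|
| 0 | 25.0 | 3.00 | 83.0% | 37.5 | 37.5 / 37.5 |
| 0.25 | 21.9 | 2.63 | 72.3% | 37.5 | 46.9 / 50.0 |
| 0.5 | 18.75 | 2.25 | 58.9% | 37.5 | 56.25 / 62.5 |
| 0.75 | 15.6 | 1.88 | 44.5% | 37.5 | 65.6 / 75.0 |
| 1 | 12.5 | 1.50 | 30.8% | 37.5 | 75.0 / 87.5 |

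**5. Added spread.** Mixing two sequences with different means also widens each training's distribution. At r = 1, additive, the between-sequence variances are 156.25 (M: 50 and 75) and 625 (L: 25 and 75), average 390.6. The SD is √(625 + 390.6) = 31.9 and power is 20.8%. In the multiplicative case the SD is 35.9 and power 17.4%.

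**6. Own-start baseline for each period.** If each training multiplies the value at the start of its period, the scores are 50 and 25 in both periods. The difference stays at 25 for any r, with power 83.0%. If gains are instead fixed amounts in study-baseline units, then at r = 1 the period-2 scores are 50/1.25 = 40 and 25/1.5 = 16.7. The means are 45 and 20.8, a difference of 24.2, so almost all of the loss is still avoided.

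**7. DXA count.** 140 / 35 = 4 scans. Start and end of each period plus follow-up, counting the baseline visits as the start of period 1, make 5 occasions: 5 × 35 = 175 microSv. Background ratio: 3000 / 140 = 21.4; 3000 / 175 = 17.1.

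**The case against.** The strongest reply is that period-specific change is what the sponsor intends. Research Design describes a pre-post crossover, assessments are scheduled at the start of each period, and the carryover check refers to change within each training period. The sentence in Statistical Analysis can be read as the baseline and the completion of each intervention. This is a fair reading and it lowers the severity. It does not remove the point: the text never says so, and its other uses of baseline point to the testing before randomisation.

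A reader might infer from the 3a summary and the four-scan total that no assessment is made after washout. The documents do not support that. The summary does not exclude other visits, and it also leaves out the six-week follow-up, which is certainly planned. Four scans would equally fit the start and end of each of two periods. The Phase 1 test list under Specific Aims does not include DXA. The scan mismatch arises because Post-training evaluation and 6-Week Follow-up evaluation repeat every baseline measure, and DXA is one of them.

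A reader might also infer that persistence of training effects is the study hypothesis, so that a large bias is to be expected. The stated hypotheses concern greater recovery and connectivity with multimodal training. They do not concern persistence through six weeks without training, and the washout is there to remove carryover.

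The reply that a per-period baseline could be left to a statistical analysis plan stands only in part. The protocol itself fixes the primary outcome and the analysed score, and it fixes them ambiguously.

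**Conclusion.** The concern holds as a moderate defect in the definition of the primary outcome and the analysed score. Taken literally, the wording biases the contrast between trainings by 12.5 points times the retained fraction. There is no bias with complete washout, a quarter of the planned difference is lost at half retention, and half is lost at full retention. Power falls from 83% to 59% and 31% with SD 25, and to about 17–21% (t-test) at full retention once the added spread is counted.

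Two conditions must both be met for any harm: the study baseline is actually used for period 2, and some gain survives the washout. The protocol settles neither, so halving is an extreme and not a forecast. The stated power and sample size are correct on their own inputs. They assume either own-start baselines or complete washout.

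The DXA discrepancy is a separate, small inconsistency in the risk text: 140 against 175 microSv, and about 21-fold against 17-fold. It has no bearing on the treatment contrast.

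**What to change.** 1. In Primary outcomes and in Statistical Analysis, state that each period's change runs from that period's own start assessment to its end, and that for period 2 the start is the assessment after washout.
2. In 3a, extend the summary so that it lists the start-of-period assessments and the follow-up, in line with Specific Aims and Post-training evaluation. It would help to give the post-washout visit a time window, since the one now stated applies only to the end of each intervention.
3. In 3b, reconcile the exposure total with the schedule: either restate it for five scans (about 175 microSv, about 17-fold) or name the visit at which DXA is not repeated.

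No covariate or change of test is needed. The cost is wording only, because the post-washout assessment is already scheduled; the radiation comparison becomes slightly less favourable if five scans are kept. An own-start baseline removes this double counting but not other forms of carryover, such as an altered response to the second training, so the period comparison should stay.

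### The primary test treats the same participants' two results as independent samples, so its standard error is wrong unless those results are uncorrelated, and the crossover's within-person precision goes uncredited

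*Protocol*

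**What the plan says.** The interventional phase is a two-sequence, two-period crossover: "participants will be randomly assigned to receive either locomotor training followed by multimodal training, or multimodal training followed by locomotor training". Each person therefore contributes two values to each primary outcome (tibialis anterior MEP amplitude and lower extremity motor score), because "outcome measures will be calculated within each subject as the percent change between baseline and completion of each intervention".

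The choice of test is justified by the statement that "The most rigorous method of analyzing data from crossover studies involves the use of independent-sample rather than paired-sample tests". The primary comparison follows: "The percent change across all subjects for each training modality will be compared using independent-sample t-tests or Mann-Whitney U tests". The check for carryover has the same form: "the percent change across all subjects for each training period (pre-washout, post-washout) will also be compared using independent sample tests". The section mentions no comparison of sequence groups, no period term and no participant effect.

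The Power Calculation paragraph uses the same independent-sample test, claims more than 80% power with 18 subjects at a two-sided 0.05, and relies on this statement: "The use of a crossover design will reduce inter-subject variability between the two training modalities compared to a parallel-group design".

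**The concern.** An independent-sample test has a proper place in a two-period crossover: its two samples are the two randomised sequence groups. The variable is then each person's difference between periods or, less efficiently, the period 1 result alone. The protocol names that kind of test but applies it to the two modalities, where every completer sits in both samples.

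Three things follow:

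- The covariance between a person's two responses is left out of the standard error.
- The randomised factor, sequence, is not used in the analysis.
- A difference between periods is not removed. It adds to residual variance and, if dropout leaves the sequences unequal, it biases the modality contrast.

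The p-values and confidence intervals of both primary outcomes are at stake. They are too cautious if responses correlate positively within a person. They are too liberal if they correlate negatively, for example if a large first-period gain leaves less room for a second.

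**Working it through.** **Inputs (Power Calculation paragraph).** Difference of 50 − 25 = 25 points: "we project an improvement of 50% with MULTIMODAL training versus 25% with TREADMILL training". Spread: "We conservatively project an estimated variance of 25% for each group". I read this as an SD of 25 points. That is an assumption, but it reproduces the stated power, whereas a literal variance of 25 (SD 5) would make the effect five SDs. Completers: 18 of 24 enrolled. Two-sided α = 0.05. The correlation ρ between a person's two percent changes is not given, so I use a range from −0.5 to 0.7.

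**Step 1. Reproduce the stated power.** Two-sample t-test, difference 25, SD 25:

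- 18 values per modality: power 83.0%, which matches the claim of more than 80%.
- 18 people split 9 against 9: power 51.3%, which does not match.

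The stated figure therefore counts 18 people as 18 + 18 independent observations. The dropout allowance is consistent: 18 / 0.75 = 24.

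**Step 2. Standard errors.**

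- Planned test: 25 × √(2/18) = 8.33, whatever ρ is.
- True: the SD of a within-person difference is 25 × √(2(1 − ρ)). Dividing by √18 gives 8.33 × √(1 − ρ).

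**Step 3. Operating characteristics.** The planned test was simulated on 18 bivariate-normal pairs, 200,000 trials per setting. The sequence-group test compares period 1 minus period 2 differences, 9 against 9 on 16 df. The two group means differ by 2 × 25 = 50, and the SD is 25 × √(2(1 − ρ)).

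| ρ | Planned SE | True SE | Type I error, planned | Power, planned | Power, sequence-group |
|---|---|---|---|---|---|
| −0.5 | 8.33 | 10.21 | 10.9% | 78% * | 63% |
| −0.3 | 8.33 | 9.50 | 8.4% | 80% * | 70% |
| 0 | 8.33 | 8.33 | 5.0% | 83% | 80% |
| 0.3 | 8.33 | 6.97 | 2.1% | 87% | 92% |
| 0.5 | 8.33 | 5.89 | 0.8% | 90% | 98% |
| 0.7 | 8.33 | 4.56 | 0.1% | 94% | 99.9% |

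\* Not comparable with the last column, because the planned test exceeds its nominal level here. The sequence-group test held 5% in every row.

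**Step 4. Period effect (illustration).** Assume every second-period response is 25 points lower, with ρ = 0.3.

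- Sequences balanced 9 and 9: the modality contrast is unbiased, but planned power falls from 87% to 80%. The sequence-group test stays at 92%.
- Dropout leaves 11 multimodal-first and 7 locomotor-first: the multimodal mean shifts by −25 × 7/18 = −9.7 and the locomotor mean by −25 × 11/18 = −15.3. The planned contrast is therefore biased by 5.6 points, while half the difference between the sequence-group means is unbiased.

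**Step 5. Carryover check.** The pre-washout and post-washout samples are again the same people, so the independence fault is repeated. The comparison also measures a difference between periods, which is not the same thing as carryover.

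**The case against.** The strongest reply is that the error probably runs in the safe direction. If people who respond well to one training also respond well to the other, ρ is positive, the test is conservative, and power still exceeds the promised 80% (87% at 0.3, 90% at 0.5). At ρ = 0 the planned test is valid and slightly more powerful than the alternative (83% against 80%). Percent change already removes differences in baseline level. Randomisation in blocks of 6 tends to balance the sequences, in which case a period effect cancels from the contrast. The protocol also requires a Bonferroni correction, which would lower the thresholds used here.

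Most of this is right and limits the size of the claim. With positive ρ the harm is lost power and over-wide intervals rather than false positives. The crossover's gain is not wholly absent: the estimate does become more precise as ρ rises, but the standard error never credits it. The correct analysis also has less power when ρ is negative, and needs 24 completers for 80% power at ρ = −0.3.

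None of this makes the test valid. Whether it errs towards caution or towards false positives depends on a quantity the protocol does not know. Balance is not assured when up to 25% may drop out, and a stricter threshold makes lost power more costly.

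**Conclusion.** The concern holds. As written, the primary test compares the same people as if they were different people, and nothing elsewhere in the protocol corrects it. It also cannot deliver the benefit that the power paragraph claims for the crossover, because its standard error ignores ρ.

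The size depends on ρ. Against a nominal 5%, the type I error runs from about 0.1% at ρ = 0.7 to about 11% at ρ = −0.5. The power given up is about 5 points at ρ = 0.3 and 8 points at ρ = 0.5.

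These figures assume an SD of 25 points, normal responses, 18 completers and α = 0.05 without the Bonferroni correction. They were worked for the MEP projection and the t-test. No figures were run for the motor score or for the Mann-Whitney version, but the structural fault is the same there. The paper that the protocol cites for its choice of test was not at hand and plays no part in this conclusion. Because the fault lies in the primary analysis, it must be corrected before the data are analysed.

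**What to change.** Replace the comparison by modality with the following:

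- For each participant, calculate the period 1 change minus the period 2 change.
- Compare these differences between the locomotor-first and multimodal-first groups with an independent-sample t-test or rank-sum test.
- Report half the difference between the group means, with its confidence interval, as the modality effect free of an additive period effect.

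A mixed model with modality, period, sequence and a participant random effect is an equivalent choice. Delete the pooled test, and describe the pre-washout against post-washout comparison as a within-person period effect rather than a test of carryover.

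Restate power for the sequence-group test, with the SD labelled as such and ρ stated as an assumption. With SD 25 and α = 0.05, 80% power needs 18 completers at ρ = 0, 14 at 0.3 and 12 at 0.5, but 24 at −0.3.

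The cost is one paragraph of analysis text and a revised power statement. No new data are needed, and no extra participants if ρ is zero or positive. If ρ could be negative, the planned 18 completers fall short of 80%, and the protocol should say so.
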